### 2.5. Anthropometric Measurements

Weight is assessed with a precision of 0.1 kg using the Weighing Scale 803 (Seca, Hamburg, Germany), while height is measured with a Stadiometer 213 (Seca, Birmingham, UK) to the nearest 0.1 cm. Children undergo measurements wearing light clothing and without shoes. BMI Z-scores are computed using Dutch and Belgium reference values [44]. The primary outcome is the absolute change in BMI Z-score, aiming for BMI scores closer to national and international standards, resulting in reduced BMI for overweight and obese children and increased BMI for underweight children. Hip and waist circumferences were gauged with a measuring tape (model 201, Seca, Hamburg, Germany) to the nearest 0.1 cm, following the World Health Organization’s assessment protocol [45]. Each anthropometric measurement was conducted twice, with a third measurement implemented if the discrepancy between the initial two measurements surpassed predefined limits (weight ≥ 0.2 kg, height ≥ 0.5 cm, hip and waist circumference ≥ 1.0 cm). These outcomes were then averaged.

### 2.6. Physical Activity Behavior

PA levels were objectively evaluated using the Actigraph accelerometer (Actigraph, GT3X+, Actigraph, Pensacola, FL, USA). The monitor was affixed to the right hip using an elastic band, and all children were instructed to wear the device continuously for seven days. The device should be worn throughout the day, excluding sleeping hours and activities involving water (such as swimming, bathing, or showering). Concurrently, parents completed a brief activity diary in the same week, detailing their child’s PA, swimming behavior, and any exceptional circumstances (e.g., the child’s illness).

Non-wear time was defined as ≥60 consecutive minutes of zero counts, allowing for interruptions of up to 2 min of counts between 0 and 100. A valid day was defined as a minimum of 480 min (8 h) of wear time, and children were included in analyses if they had at least three valid weekdays and one valid weekend day. Days not meeting these criteria were classified as invalid and excluded from analyses. When accelerometer data were incomplete but accompanied by diary notes explaining non-wear reasons, these days were recorded but remained excluded from accelerometer-derived outcomes. Average daily counts, sedentary time, and moderate-to-vigorous PA (MVPA) were derived only from valid days.

The Physical Activity Questionnaire for older children (PAQ-C) was surveyed to assess overall levels of PA during greening [46]. The PAQ-C is appropriate for elementary school children (approximately 8–14 years old) who are currently in a school system and have regular recess as part of their school week. It is a validated questionnaire with a 7-day look-back period that assesses general moderate to vigorous physical activity levels measured during the school year. The PAQ-C provides a summary PAscore derived from nine items each rated on a 5-point scale with 1 being the lowest activity score and 5 being the highest activity score. This questionnaire was administered at T0, T12 and T18.

### 2.7. Cognitive Performance

To assess cognitive effects, five computerized tests were administered using the Mindsware test manager (Bureau Mindsware, Den Helder, The Netherlands), guided by trained staff [47]. The continuous performance test (CPT) evaluated attention and impulsivity by requiring responses only to specific stimulus combinations (e.g., X after A). The symbol digit modalities test (SDMT) assessed information processing via symbol-number matching. The SPANNE test measured short-term memory by having children repeat number sequences forward and backward. The signal detection test gauged visual processing speed by identifying deviant symbols in a series. Lastly, the STROOP task tested cognitive control by having participants name the ink color of incongruent color words.

### 2.8. Particulate Matter Determination in Urine

The exposure to fine particulate matter was measured using an internal exposure marker, black carbon, employing a specific and sensitive detection technique. Measurement was based on the white light generation of carbon particles under femtosecond pulsed illumination, as previously developed, validated, and applied in human biomonitoring studies [48,49]. This in-house developed and validated technique enables label-free measurement of black carbon concentrations in urine, reflecting the internal accumulation of medium to chronic exposure to traffic-related air pollution. Urine samples collected per grade level were pooled into one sample per assessment time point, both for the control and intervention schools. 100 μL urine sample was loaded per imaging chamber, constructed by placing a coverslip (24 × 24 mm) onto a microscope slide (75 × 25 mm), joined with 100 μm thick double-sided tape. The urine-filled imaging chambers were sealed airtight to prevent dehydration. Images of the urine samples were captured at room temperature at nine different locations within the imaging chamber using a Zeiss LSM880 confocal microscope (Carl Zeiss Microscopy GmbH, Jena, Germany). A peak-finding algorithm was applied to determine the number of black carbon particles in the images. The average amount of detected particles in the various images was normalized to the osmolality of the measured samples. Ultimately, the result was expressed as the number of detected black carbon particles per milliliter of urine. A formal limit of detection cannot yet be established for this optical method, as no certified reference materials with known black carbon particle counts exist. Nevertheless, prior studies demonstrate that the technique is sufficiently sensitive and reproducible to detect differences in internal black carbon exposure in human samples [48,49].

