### 2.10. Data Analysis

Linear mixed model analysis will be employed to evaluate the longitudinal impact of the intervention on the primary outcomes, absolute BMI Z-scores, change in cognitive function, change in well-being, and change in black carbon levels. Data will be analyzed using linear mixed models, performed in IBM SPSS Statistics for Windows (version 28.0.1.1, Armonk, NY, USA: IBM Corp). This approach addresses correlations within individuals inherent in repeated-measures research designs. Its advantage lies in handling missing values naturally through a likelihood-based method, assuming data are missing at random.

The fixed part of the model incorporates group (intervention vs. control), time (measurement time points), the interaction term group*time, and country (Belgium/The Netherlands). Baseline variables linked to missing data or outcomes will also be included for unbiased and precise results. To account for the correlation between repeated measurements several covariance structures (including random effects if necessary) will be considered. The best covariance structure for the repeated measurements will be chosen based on Akaike’s Information Criterion. The analysis will encompass all participants with at least one outcome measurement. Because several measurements were collected only in Belgian or only in Dutch schools, the resulting missingness is structured and not at random. Linear mixed models are used because they accommodate unbalanced data and allow all available observations to be included without listwise deletion. Country will be included as a fixed effect in all models to control for systematic differences between the Belgian and Dutch school contexts. For outcomes collected in only one country, analyses will be conducted within that specific subsample and reported separately. In addition, sensitivity analyses will be performed to examine whether excluding country-specific measures affects the direction or magnitude of findings for outcomes measured in both countries.

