A key advancement of this study is its ability to explore potential mechanisms underlying these health effects by integrating ecological, behavioral, cognitive, and environmental exposure data within a single protocol. Whereas most previous school-greening studies focused solely on behavioral or psychological outcomes, this study combines detailed biodiversity assessments, objective PA measurements, cognitive testing, and biomarkers of internal black carbon exposure. This multidimensional approach allows examination of whether increased biodiversity is associated with changes in cognitive functioning via restorative and stress-reduction pathways, and whether greener schoolyards may mitigate children’s internal exposure to airborne pollutants by altering microenvironmental conditions. By linking ecological features of the schoolyard to both cognitive and physiological markers, this study provides the opportunity to investigate mechanistic pathways that have rarely been tested empirically in school settings.

Though limited by its non-randomized design, the inclusion of schools from Belgium and The Netherlands enhances generalizability. A comprehensive set of outcome measures—anthropometric data, cognitive assessments, questionnaires, and activity monitoring—supports a robust analysis. Due to the modest sample size, the study is considered an exploratory study aimed at informing future, larger-scale research.

Challenges include school-specific logistical barriers, reliance on some self-reported data, and the need for long-term maintenance. Future studies should incorporate more objective data and extended follow-up periods.

While previous research has evaluated green schoolyards [58,59,60,61], the present study is distinguished by its focus on biodiversity and novel outcomes such as black carbon exposure and cognitive functioning. Comparisons with a comprehensive school health program that includes PA and nutrition [18] offer deeper insights into the potential of biodiverse schoolyards.

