## Figures and Tables

**Figure 1 ijerph-22-01805-f001:**
[figure not shown]
Map of Intervention and Control School Locations in the Study Region.

**Table 1 ijerph-22-01805-t001:** Overview of questionnaires and measurements for data collection measures within the Green Healthy Elementary School of the Future initiative.

Data Collection Activity	Parents	Children	Time Point
General questionnaire			
Personal data (birth data, sex, ethnicity, addresses, parity, SES, education level of the parents)	x		T0
Sleep ^1^	x		T0, T6, T12, T18
School absenteeism ^1^	x		T0, T6, T12, T18
Household smoking habits	x		T0, T6, T12, T18, T24
Visits to GP, disease status ^3^	x		T0, T6, T12, T18
Quality of life (parental PedsQL) ^1^	x		T0, T6, T12, T18
PA behavior	x		T0, T6, T12, T18
Food + water consumption, habits and preferences ^1^	x	x	T0, T6, T12, T18
Strengths and difficulties questionnaire (SDQ)	x		T0, T6, T12, T18, T24
Kidscreen-52		x	T0, T6, T12, T18, T24
Physical Activity Questionnaire for Children (PAQ-C)		x	T0, T12, T18
Bullying behavior		x	T0, T6, T12, T18, T24
Knowledge, perception and valuation of biodiversity		x	T0, T12, T18, T24
Height		x	T0, T12, T18, T24
Weight		x	T0, T12, T18, T24
Waist/hip circumference		x	T0, T12, T18, T24
Physical activity using Accelerometer (Actigraph, GT3X+, Actigraph, Pensacola, FL, USA) ^2^		x	T0, T12, T18
Cognitive tasks and eye-tracking		x	T0, T6, T12, T18, T24
Particulate matter determination in urine ^3^		x	T0, T6, T12, T18, T24

^1^ Measurements only performed in Dutch schools. ^2^ Measurements only performed in intervention schools. ^3^ Measurements only performed in Belgian schools. Due to practical reasons T6 and T24 measurements could not be performed in Dutch primary schools. T0: November 2021, T6: May 2022, T12: November 2022, T18: May 2023, and T24: November 2023.

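### Black carbon is listed as a primary outcome of a child-level mixed model, but the urine was pooled and taken only in Belgium, so no child has a value and each arm is one school

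*Protocol article*

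**What the plan says.** Section 2.10 sets out a linear mixed model for "the primary outcomes, absolute BMI Z-scores, change in cognitive function, change in well-being, and change in black carbon levels". It describes the model as one for children measured repeatedly: "This approach addresses correlations within individuals inherent in repeated-measures research designs". The analysis set is also defined by child: "The analysis will encompass all participants with at least one outcome measurement". The fixed part holds group, time, their interaction and country, plus baseline variables related to missingness or outcome.

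Section 2.8 describes the urine differently: "Urine samples collected per grade level were pooled into one sample per assessment time point, both for the control and intervention schools".

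In Table 1 the row "Particulate matter determination in urine ^3" carries the footnote "Measurements only performed in Belgian schools". The row lists five visits, T0 to T24. The missing T6 and T24 visits concern only the Dutch schools, so all five stand for Belgium. Each country has one intervention and one control school.

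Section 2.10 also says that an outcome collected in one country will be analysed and reported within that country. It omits school random effects because there are only four schools, and relies on the country term to take up the school effect.

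On primary status, Section 2.5 says "The primary outcome is the absolute change in BMI Z-score", and the Abstract likewise marks only BMI z-score as primary.

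**The concern.** The model in Section 2.10 needs several values per child and makes use of child-level covariates. Pooled urine gives neither: the measured unit is a pool, and no participant meets the analysis-set definition for this outcome. The article does not say how the two sections fit together.

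The Belgian restriction adds a second difficulty. Inside that subsample the group contrast is a contrast between two schools, so a local change in traffic or building work near either school cannot be told apart from greening. The country term, which is meant to stand in for school, takes a single value there.

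At stake is a p-value for an outcome called primary that the design cannot support. The conflict over which outcomes are primary makes it harder for a reader of the results to know how much weight that p-value was meant to carry.

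**Working it through.** **The plan's own figure.** Section 2.9 gives a detectable standardized effect of 0.52 to 0.63 with 40 to 60 children per group, 80% power and α = 0.05 (sidedness not stated; two-sided assumed). For two independent groups of n children, d ≈ (1.960 + 0.842) × √(2/n).
- n = 60: 2.802 × 0.1826 = 0.51 (t-based: 0.516)
- n = 40: 2.802 × 0.2236 = 0.63 (t-based: 0.634)

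The figure reproduces. It rests on independent child-level values, which black carbon does not have.

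**Inputs for black carbon.** Belgian schools: 2, one per arm (Sections 2.1 and 2.10, Table 1). Visits: 5 (Table 1). Grades per school: not stated; 4 to 6 is assumed from the eligible ages of 7 to 12.

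**Columns of the fixed part.** Intercept 1 + group 1 + time 4 + group-by-time 4 + country 1 = 11. In Belgium alone, country is constant and duplicates the intercept, so the rank is 10. The country term adjusts for nothing.

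**Number of values.** The pooling sentence can be read in two ways.

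| Reading | Values | Rank | Residual df |
|---|---|---|---|
| One pool per school and visit | 2 × 5 = 10 | 10 | 0 |
| One pool per grade, 4 grades | 2 × 4 × 5 = 40 | 10 | 30 |
| One pool per grade, 5 grades | 2 × 5 × 5 = 50 | 10 | 40 |
| One pool per grade, 6 grades | 2 × 6 × 5 = 60 | 10 | 50 |

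On the first reading the fit is saturated and group-by-time has no standard error. On the second, a model with the pool as unit can be fitted, but its 30 to 50 degrees of freedom are nominal. All pools in an arm share one school, so there are no between-school degrees of freedom. On both readings the number of child-level values is 0.

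**Grade as a repeated unit.** Enrolment closed in November 2021 and visits run to November 2023. Assuming yearly promotion, the same grade at T0, T12 and T24 holds different children. Change in a grade's pool across school years is then not change within children, unless pools are followed by cohort.

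**The case against.** Several points can fairly be made for the plan.
- The study is declared exploratory, and the Abstract and Section 2.5 make only BMI z-score primary. One sentence in Section 2.10 creates the conflict. This stands, and it makes the correction easy. It does not settle the unit of analysis.
- Section 2.10 provides for separate analysis of single-country outcomes. This covers the country restriction but not the pooling, nor the fact that group then equals school.
- One school per arm and country is a limit of the whole design, and the Discussion admits non-randomization and potential confounding. This is true. For black carbon, however, there is no second pair of schools and the country term drops out.
- On the per-grade reading a mixed model can be run, and nothing says that pool values would be assigned to children. Both points stand. The model would still not be the one described.

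A reader might infer three stronger points that the documents do not support.
1. That the Discussion promises to link black carbon to a child's cognition. The phrase "By linking ecological features of the schoolyard to both cognitive and physiological markers" ties schoolyard features to each kind of marker separately, not the markers to each other.
2. That Table 1 should have a row for schoolyard biodiversity. Section 2.2 says that the table covers measures taken in children and parents or caregivers.
3. That pooling raises the detectable effect from 0.52–0.63 to about 1.8–2.0. With 5 or 6 independent pools per arm at one visit, the detectable difference is indeed 2.02 or 1.80, but in pool-level SDs. A pool of k children has an SD near 1/√k of the child SD if there is no extra between-grade variance. As an illustration, assume 20 Belgian children per arm in 5 pools, so k = 4. Then 2.02/√4 = 1.01 child SDs, against 0.91 for individual samples from the same 20 children. The two scales cannot be compared directly.

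**Conclusion.** Wrong as written. The child-level mixed model that Section 2.10 specifies for black carbon cannot be applied to the data that Section 2.8 describes, and the primary label conflicts with the Abstract and Section 2.5.

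The size depends on a pooling unit that the article leaves ambiguous: 10 values with no residual degrees of freedom, or 40 to 60 values if pools were kept by grade (4 to 6 grades assumed). The absence of child-level values, the single school per arm and the constant country term hold on either reading. The detectable effect in Section 2.9 is correct for 40 to 60 independent children per group and does not carry over to this outcome. The point about changing grade membership rests on the assumption of yearly promotion.

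**What to change.** - In Section 2.10, remove black carbon from the primary outcomes, in line with the Abstract and Section 2.5.
- In Section 2.8, state whether a pool is one school or one grade within a school at each visit, and give the number of pools.
- Take the pool as the unit of analysis. Use no child-level covariates, and do not assign pool values to children.
- Report the results descriptively as one Belgian intervention school against one Belgian control school, with no p-value attributed to greening.

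This needs a change of wording and a simpler analysis, and no new data. The cost is that black carbon becomes a descriptive secondary outcome.

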### 2.9. Number of Participants

Due to the explorative nature of the study (hypothesis generating), no detailed sample size calculations are performed. The aim is to include 150–200 participating children from the participating schools in The Netherlands and Belgium. To account for missing data (assumed to be around 20%), the effective sample size for the analysis might vary between 80 and 120 children (40 to 60 per group). Based on 80% power and a significance level α of 0.05, standardized effect sizes (Cohen’s) between 0.52 and 0.63 can be detected with these expected sample sizes. This study was approved by the commission for Medical Ethics of Hasselt University (CME2021/042) and is a part of the original HPSF trial (METC-Z no. 14-N-142).

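### 150–200 children less about 20% is 120–160, not 80–120, and the single detectable-effect range does not carry over to one-country visits and outcomes

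*Protocol article*

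**What the plan says.** Section 2.9 of the protocol article calls the study exploratory and says that it makes no detailed calculation. It then gives a chain of figures:

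- Enrolment: "The aim is to include 150–200 participating children from the participating schools in The Netherlands and Belgium".
- Missing data and analysable number: "To account for missing data (assumed to be around 20%), the effective sample size for the analysis might vary between 80 and 120 children", that is, 40–60 in each group.
- Power: "Based on 80% power and a significance level α of 0.05", with sidedness not given.
- Detectable effect: "standardized effect sizes (Cohen’s) between 0.52 and 0.63 can be detected with these expected sample sizes".

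No other source of loss is named between the enrolment target and the analysable number, and the detectable range is not limited to particular outcomes or visits.

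The footnotes to Table 1 restrict coverage: "Due to practical reasons T6 and T24 measurements could not be performed in Dutch primary schools". They also mark sleep, school absenteeism, parental PedsQL and food and water consumption as Dutch only, and GP visits with disease status and urinary particulate matter as Belgian only. Section 2.10 analyses outcomes collected in one country within that country alone. It also names change in black carbon among the primary outcomes. Section 2.8 says that urine was pooled by grade level at each time point.

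**The concern.** Section 2.9 is the only place where the article says what size of effect the study can detect, and its figures do not follow from one another. The upper end of the stated analysable range (120) is the lower end of the range that the stated enrolment and missing-data rate produce. A reader cannot tell whether the planners expected 20% loss, roughly twice that, or a smaller intake.

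The second part concerns scope. The 24-month visit, which includes the last height and weight measurements for BMI z-score, has data from the Belgian schools only, and several outcomes exist in one country only. A reader who judges a null result there against 0.52–0.63 would be using a figure that assumes 40–60 measured children per group.

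**Working it through.** **Inputs** (Section 2.9): enrolment 150–200; missing about 20%; analysable 80–120, equal groups of 40–60; power 80%; α 0.05; d 0.52–0.63.

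**1. Reproduce the stated effect sizes.** For a two-group comparison of means with n per group, the normal approximation is d = (1.96 + 0.84) × √(2/n). The exact t-test gives slightly larger values.

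| n per group | d, normal, two-sided | d, t-test, two-sided | d, t-test, one-sided |
|---|---|---|---|
| 20 | 0.886 | 0.909 | 0.801 |
| 30 | 0.723 | 0.736 | 0.650 |
| 40 | 0.627 | 0.634 | 0.561 |
| 60 | 0.512 | 0.516 | 0.457 |
| 80 | 0.443 | 0.446 | 0.395 |

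The two-sided t-test at 40 and 60 per group gives 0.63 and 0.52, as stated. As a check, power is 79.5% at d = 0.63 with 40 per group and 80.6% at d = 0.52 with 60 per group. The one-sided test does not reproduce the figures. So the effect sizes are right for 40–60 per group.

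**2. Try to reproduce the analysable number.**

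- 20% removed: 150 × 0.8 = 120; 200 × 0.8 = 160. Range 120–160, or 60–80 per group.
- Division by 1.2: 150/1.2 = 125; 200/1.2 ≈ 167.
- 20% removed twice: 150 × 0.64 = 96; 200 × 0.64 = 128.

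None of these gives 80–120. From the table, 60–80 per group corresponds to d of 0.52–0.45.

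**3. What would give 80–120?**

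- Keep 20% loss and change enrolment: 80/0.8 = 100 and 120/0.8 = 150. Enrolment of 100–150 reproduces both ends exactly.
- Keep enrolment and change the loss, pairing low with low and high with high: 1 − 80/150 = 46.7% and 1 − 120/200 = 40%.
- With the ends crossed: 1 − 120/150 = 20% and 1 − 80/200 = 60%.

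The article gives no ground for choosing among these.

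**4. One-country visits and outcomes.** No country split is given. Assume an equal split between countries and equal groups within each.

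| Analysable total | Per group in one country | d (t-test, two-sided) |
|---|---|---|
| 80 | 80/4 = 20 | 0.91 |
| 120 | 120/4 = 30 | 0.74 |
| 160 | 160/4 = 40 | 0.63 |

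On the stated 80–120, power with 20–30 per group is 36–51% at d = 0.52 and 49–67% at d = 0.63. If the country analysed holds one third to two thirds of the 80–120 children, d runs from 1.13 (80 children, one third) to 0.63 (120 children, two thirds).

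These are simple two-group calculations that ignore repeated measures. They do not apply to black carbon, where the unit is a pooled grade-level sample and not a child.

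**The case against.** The strongest reply is that Section 2.9 disclaims precision. The study is declared exploratory, the figures are hedged, no decision rule in the article rests on them, and the Discussion concedes the modest sample and limited power. For two-country visits the slip is conservative, since 120–160 children would detect smaller effects than those printed. All of this stands, and it lowers the priority. It does not make the printed figures consistent: declining a formal calculation is different from printing one whose steps disagree.

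Three stronger readings are tempting, and the documents do not support them.

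- A reader might infer that 40–47% loss was really expected. That holds only if the enrolment target is right and the ends are paired low with low. An intake of 100–150 at 20% loss fits equally well.
- A reader might infer that every one-country analysis is less sensitive than stated. On 120–160 analysable children with an equal split, the range is 0.74–0.63, and its better end meets the stated 0.63. The planned mixed models also use repeated measurements. With an assumed baseline correlation of 0.8, adjustment would multiply d by √(1 − 0.8²) = 0.6, so 0.91–0.74 becomes about 0.55–0.44. The same factor would shrink the two-country figures, so the relative gap remains, but the absolute level is not established.
- A reader might want to put a number on clustering by school. The article gives no intracluster correlation, so no number can be defended. Section 2.10 openly omits school random effects because there are only four schools. What can be said is that the printed d takes no account of clustering.

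**Conclusion.** The point holds in two parts.

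First, the enrolment target, the missing-data rate and the analysable number contradict one another. This needs no assumption. On the stated enrolment and loss, the analysable number is 120–160 and d is about 0.52–0.45, against the stated 80–120 and 0.52–0.63. Which of the three figures is wrong cannot be told from the article.

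Second, the detectable range is stated without restriction but does not carry over to visits and outcomes covered in one country only. The size of the gap rests on the assumed equal country split and a simple two-group comparison: about 0.91–0.74 on the stated analysable number, or 0.74–0.63 on 120–160.

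This should be fixed, but it is not critical. It affects how results, especially null results, are read. It is no evidence that the two-country analysis is underpowered relative to what the article claims.

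**What to change.** In Section 2.9, reconcile the three figures. Enrolment closed in November 2021 (Section 2.1), so the best course is to replace the target range with the number actually enrolled, state the loss assumed from it, and recompute d. If the range is kept, change whichever of enrolment, loss or analysable number was misstated so that the arithmetic closes.

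Then add:

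- that d refers to a two-sided, two-group comparison of child-level outcomes at visits covered in both countries, and takes no account of clustering by school;
- a separate line for T6, T24 and the one-country outcomes, computed from the actual number of children in the country concerned;
- that the child-level d does not apply to black carbon, because urine was pooled by grade level.

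The cost is wording only, with no change to data collection or analysis. The figure for one-country analyses will probably look less favourable than the one now printed.
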